### Outcomes

Initially, all participants will be interviewed and evaluated in relation to the degree of osteoarthritis and functionality. Information regarding the patient data will be confirmed
*via* interview, considering data such as complete name, date of birth, age, affected knee(s), duration of pain, arterial blood pressure, list of medications in use, consumption of tobacco or alcohol, associated diseases, if they are undergoing physiotherapy treatment or regular physical activity.

The classification regarding the degree of osteoarthritis will be performed by analyzing the radiograph of the affected knee according to the method of Kellgren and Lawrence. The radiographs will be analyzed, the degree of osteoarthritis will be identified with the negatoscope support, and the images in the digital form will be displayed on a computer screen, considering the classification expressed in degrees ranging from zero to IV.

Subsequently, the identification of functionality will be assessed according to the Brazilian version of the Knee Injury and Osteoarthritis Outcome Score (KOOS). The KOOS questionnaire was developed in the 1990s as an instrument to evaluate the patient’s perception of their knee and associated problems. Since its first publication in 1998, the psychometric properties of KOOS were evaluated in a systemic review of 37 articles demonstrating adequate validity in its use for the study population.
^
37
^

Regarding the pre- and post-intervention assessment instruments, all participants will have the following parameters evaluated: concentration of MMP-3 and GPx, pain, edema, flexibility, and self-perception of the general well-being. In addition, it should be noted that in the 24-hour-follow-up, only the biochemical concentrations and the self-perception questionnaire will be reevaluated.

The biochemical variables will be measured in peripheral blood from the concentrations of MMP-3 and GPx. The levels of MMPs will be measured based on the Enzyme-Linked Immunosorbent Assay (ELISA) methodology, which is based on the antigen-antibody interaction and will be performed according to the kit manufacturer’s instructions. MMP-3, a constituent of the stromelysin family that is an important mediator responsible for the degradation of collagen type II, IX, and XI,
^
12
^
^,^
^
13
^ will be considered for this analysis. Oxidative stress will be measured by analyzing the peripheral blood from percutaneous punction. The sample collection time will be performed according to the study by Nascimento
^
34
^ and will be in accordance with the following times: T0 (immediately before the intervention), T1 (immediately after the intervention), and T2 (24 hours after the intervention).

The assessment of the degree of pain will be performed using the visual analogue pain scale,
^
38
^ from a scale graduated from zero to 10, in which zero corresponds to cases without pain and 10 corresponds to the worst imaginable pain.

The assessment of edema will be performed based on the measurement of the circumference of the affected knee(s). The measure will be performed with the patient relaxed in dorsal decubitus and the circumference will be determined with the knee in extension, based on the proximal distance of 1 cm from the base of the patella.
^
39
^ For that, the same measuring tape will be used for all measurements.

The flexibility will be assessed by measuring the amplitude of the active and passive movement for the knee flexion and, for that, a conventional goniometer will be used. The goniometer will be used because it has a low cost, is easy to handle, allows the assessments to be performed quickly, and the measurements and movement amplitude for the knee joint are valid and reliable.
^
40
^ For the assessment, the knee will be free of clothing, and the patient will be positioned in dorsal decubitus with the hip articulation at 90° of flexion. The fixed arm of the goniometer will be positioned parallel to the thigh with an orientation towards the greater trochanter of the femur and the mobile arm will be parallel to the lateral face of the fibula, directed towards the lateral malleolus. The movement reading will be performed while maintaining the final possible position of the arc of movement where the highest reading degree represents the assessed measurement.
^
41
^ All procedures will be performed by a single physiotherapist.

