### Statistical analysis

The resulting data will be tabulated, considering the absolute values and their respective standards. Information regarding the main outcome corresponding to the variations in the concentrations of MMP-3 and GPx in peripheral blood due to three different aquatic physiotherapy interventions will be comparatively evaluated among the distinct interventions and among the different times (in pre- and post-intervention moments).

The information on the outcome regarding pain, edema, and flexibility will be comparatively assessed among the different types of intervention. Statistical analyses will be performed in the SPSS software and will be considered as a significance level when p>0.05 through the repeated measures ANOVA statistical test.

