Therefore, using the physical principles of the water becomes a great ally when aiming to treat individuals in this environment. For example, floating can reduce pain in patients with osteoarthritis since immersion is directly related to the reduction of body weight. In this situation, decreasing load means reducing articular pain, allowing a patient with osteoarthritis to perform exercises where the body weight variations can be constituted as an important therapeutic strategy for performing functional exercises, which is hard to adapt to the ground.
^
24
^

The hydrostatic pressure is directly related to the immersion depth, which has a positive effect on venous blood return and reduction of edema.
^
26
^ Water can retain the temperature and is an important thermal conductor capable of transferring thermal variations to the immersed body. The aquatic physiotherapy programs performed at temperatures ranging from 33.5-35.5°C allow heat transfer to the segments in contact with water and pain relief.
^
52
^

Widely used, aquatic exercises provide positive results in joint mobility and muscle strength because, with the immersion, the impulsion force provided by floating reduces the weight of body segments in a directly proportional way to the volume of displaced water, and this condition favors the movement of individuals with muscle weakness.
^
53
^

Benefits such as an improvement of functionality, muscle strength, and quality of life are observed in patients with osteoarthritis and other skeletal muscle disorders after aquatic physiotherapy.
^
52
^ The implementation of treatment programs for knee osteoarthritis can also be planned from high-intensity exercises. This option of intervention is from adjustments in variables such as the increase in the period of training (weeks, months), frequency (days, weeks), session (minutes), or the amount of effort generated with the activity (heart rate, effort). This way, the composition of a program of high-intensity
*versus* low-intensity must take into consideration the performance of the same program of exercises or physical activity in both groups, however, with different intensities.
^
47
^

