^ In this context, the analysis of biochemical markers constitutes a relevant topic of study by evaluating the effects of different modalities of aquatic physiotherapy on the functional and biochemical behavior of patients with knee osteoarthritis and becomes more relevant when seeking understanding and answers obtained in different work intensity programs on articular cartilage. The expected results with one single session will be indicative for future longitudinal studies based on assertive intervention proposals regarding protocols with lower production of biochemical agents responsible for collagen degradation.

Finally, immersion-based physiotherapeutic treatment can prevent cartilage degeneration, inhibit inflammation, and prevent subchondral bone loss, as the presented evidence indicates that this modality can improve pain, stiffness, joint dysfunction, and muscle weakness in patients with knee osteoarthritis. Similarly, various treatment options are characterized by exercises of different intensities, such as aerobic exercises or strength training.
^
59
^ Thus, the expected results in this protocol may support future longitudinal studies, contributing to assertive intervention proposals and constituting protocols aimed at reducing the production of biochemical agents responsible for collagen degradation.

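### MMP-3 just after the session is compared between programs as a raw concentration, so part of any difference may be plasma volume change rather than marker release

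*Protocol article*

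**What the plan says.** All points are from the protocol article.

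- **Measure (Outcomes).** "The biochemical variables will be measured in peripheral blood from the concentrations of MMP-3 and GPx". MMP-3 is assayed by ELISA according to the kit instructions. For GPx only peripheral blood is named; matrix and unit are not given.
- **Timing (Outcomes).** Blood is drawn at "T0 (immediately before the intervention), T1 (immediately after the intervention), and T2 (24 hours after the intervention").
- **Comparison (Statistical analysis).** For the main outcome, "variations in the concentrations of MMP-3 and GPx in peripheral blood due to three different aquatic physiotherapy interventions will be comparatively evaluated" among programs and among times, by repeated measures ANOVA.
- **Programs (Interventions).** Program A keeps the water at shoulder height with effort at Borg 6-9. Program B keeps it at about xiphoid level in the standing exercises, at Borg 10-14. Program C follows B's exercise sequence at Borg 15-18.
- **Physiology (Discussion).** "The hydrostatic pressure is directly related to the immersion depth, which has a positive effect on venous blood return and reduction of edema".

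The measurements listed before and after each session are MMP-3, GPx, pain, edema, flexibility and self-perceived well-being. The article mentions no hematocrit, hemoglobin or other reference for blood or plasma volume. The limitations paragraph covers other biomarkers, systemic versus intra-articular sampling, interlaboratory variability and acute versus long-term effects, but not this issue.

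**The concern.** A concentration is an amount divided by a volume. If plasma volume changes during the session, the MMP-3 concentration changes even when none is released or cleared. T1 is the draw most exposed to this because it comes straight after the session.

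The protocol's own statement ties hydrostatic pressure, and through it venous return and edema, to depth. Depth differs between A and B, and effort differs across all three programs. Equal plasma volume effects therefore cannot be taken for granted. An unequal effect belongs to the program, so randomized order, wash-out and within-person comparison leave it in place. The reference group does the same programs and cannot separate it either.

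What is at stake is interpretation. The Discussion expects the results to guide future work on "protocols with lower production of biochemical agents responsible for collagen degradation". A raw T1 difference supports a statement about production only if plasma volume is stable, equal across programs or corrected for. A T0-to-T1 change within one program is open to the same doubt even when the programs do not differ.

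**Working it through.** **The plan's own figure.** The plan gives no figure on plasma volume. Its only design figure is a power of 0.95 at non-centrality 3.8. With the stated df of 16.143 and a two-sided 5% level (assumed), I obtain 0.946. That figure concerns sample size, not bias, and nothing below depends on it.

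**Step 1: size of the artefact.** Let p be the proportional change in plasma volume from T0 to T1, with the circulating amount of marker unchanged. Then

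concentration T1/T0 = 1/(1 + p)

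and the spurious ratio of program C to program A is

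(1 + p_A)/(1 + p_C).

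The documents give no value for p. The values below are assumptions, chosen to include no difference. Negative values in C are only an example of a direction.

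| p in A | p in C | gap (points) | spurious C/A |
|---|---|---|---|
| equal | equal | 0 | 1.000 |
| 0% | -5% | 5 | 1/0.95 = 1.053 |
| 0% | -10% | 10 | 1/0.90 = 1.111 |
| +5% | -10% | 15 | 1.05/0.90 = 1.167 |
| 0% | -15% | 15 | 1/0.85 = 1.176 |

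A gap of 0 to 15 points thus gives a spurious difference of about 0% to 18%. If the signs are reversed, so is the direction of the artefact.

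**Step 2: a shared shift.** If every program changes plasma volume by -10%, the between-program ratio is 1.000. Each program would still show a T0-to-T1 rise of 1/0.90 - 1 = 11.1% with no release. The pre-post comparison stays exposed.

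**Step 3: what this could do with 15 participants.** As a simplification of the planned ANOVA, take a paired t test of C against A on the log change, with n = 15, df = 14 and a two-sided 5% level. The non-centrality is ln(ratio)/SD × √15. The SD of the paired log difference is not in the documents, so three values are assumed. Example: ln(1.053) = 0.051; 0.051/0.20 = 0.26; 0.26 × 3.87 ≈ 1.0, which gives a rejection rate of 0.153.

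| spurious C/A | SD 0.10 | SD 0.20 | SD 0.30 |
|---|---|---|---|
| 1.000 | 0.05 | 0.05 | 0.05 |
| 1.053 | 0.456 | 0.153 | 0.095 |
| 1.111 | 0.966 | 0.476 | 0.245 |
| 1.176 | 1.000 | 0.833 | 0.497 |

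These are rates of declaring a program difference when production does not differ. They show sensitivity to the assumptions and are not estimates for this trial.

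**Step 4: effect of correction.** Multiplying the T1 concentration by (1 + p) gives [1/(1 + p)] × (1 + p) = 1 in each program. The spurious ratio returns to 1.000 and the rejection rate to 0.05, provided that p is measured well.

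**The case against.** **Silence in a condensed article.** Matrix, units and normalization are laboratory details that an article may leave to the full protocol, and the data collection form sits in extended data not shown here. The sentence "The resulting data will be tabulated, considering the absolute values and their respective standards" is about tabulation and is too unclear to rule out a correction. This stands in part: one can say only that no volume reference is mentioned, not that none will be taken. The point survives because the remedy needs a reading at the draw. If it is not taken then, no later analysis plan can recover it.

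**Mechanism and direction.** The Discussion speaks of venous return and edema, not of plasma volume, and says nothing about what hard exercise does to it. A reader might infer that the bias makes low intensity look better for cartilage. The documents do not support that, because they fix no direction.

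**Size.** A reader might also posit shifts of opposite sign, from +5% in A with -5% in C up to +10% with -15%. The changes from T0 would then lie 10.1 to 26.7 points apart. That range presumes opposite signs and leaves out small or zero gaps. All programs use one pool held at 33-34°C, so part of the shift may be common to them. This objection stands, and the range in the working therefore starts at zero.

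**GPx.** It is tempting to extend the point to both markers. Since the matrix and unit of GPx are not stated, that goes too far. If GPx is measured in red cells or per gram of hemoglobin, a plasma volume correction could introduce error.

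**Aim.** The Introduction sets out to identify variations in concentration, and the wording about lower production looks ahead to later studies. That is fair, and it is why raw concentrations should still be reported.

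**Conclusion.** The point holds for MMP-3 at T1. A raw concentration drawn straight after sessions of different depth and effort cannot by itself distinguish marker release from a change in plasma volume. Neither the crossover nor the reference group resolves this.

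Under an assumed gap in plasma volume change of 0 to 15 points, the spurious between-program difference is about 0% to 18%. A shift common to all programs affects only the pre-post comparison. Two assumptions carry the arithmetic: the circulating amount of marker is constant, and the plasma volume values lie in the range shown. T2 is probably less affected, although the documents give no figure for it.

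The documents do not show that a bias will occur, that it favors one program, or that GPx shares it. This is a cheap improvement to a trial that is listed as not yet recruiting. It does not invalidate the design.

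**What to change.** **Outcomes section**
- Read hematocrit (Hct, as a fraction) and hemoglobin (Hb) on the blood already drawn at T0, T1 and T2 of each session.
- State the matrix and unit of GPx.

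**Statistical analysis section**
- Derive the plasma volume change from the same session's T0. With the circulating hemoglobin mass taken as constant, blood volume scales as Hb0/Hb1 and plasma is the fraction 1 - Hct. So 1 + p = (Hb0/Hb1) × (1 - Hct1)/(1 - Hct0), and likewise for T2.
- Report corrected MMP-3, that is raw × (1 + p), beside the raw concentration, as a pre-specified sensitivity analysis of the between-program and pre-post comparisons.
- Apply the correction to GPx only if it is a plasma or serum concentration, not if it is measured in red cells or per gram of hemoglobin.
- Interpret a program difference as a difference in production only if it persists after correction.

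**Cost.** A small extra blood volume, one routine reading per draw, and possibly an ethics notification, since the Protocol amendments section sends changes that might affect the study's execution back to the Ethics Committee. No extra puncture or visit is needed.

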### Interventions

The subjects of this study will be submitted to different interventions of aquatic physiotherapy systematized as follows: program A (low-intensity protocol), program B (medium-intensity protocol), and program C (high-intensity protocol).

The access to the immersion will be from a ladder, and a period of 5 minutes will be allowed for acclimatization to the liquid environment. Considering that the intervention proposals aim to provide different levels of articular overload, the speed and time of execution will be gradually variable.

Program A will use the principles of Ai Chi
^®^ as this model is defined as a strategy of low intensity and consists of a sequence of slow movements.
^
42
^ For that, a sequence of adapted exercises
^
43
^ will be performed, according to
Table 1.

**Table 1. T1:** Program A: low-intensity protocol. The individuals in the images are students of the Physiotherapy course who consented and authorized their image.

Exercise	Periodization	Description
[figure not shown]	**4 minutes**	Antero-posterior and latero-lateral walk.
[figure not shown]	**4 minutes, 2×2 minutes**	Horizontal adduction and abduction of the shoulders alternately with rotation of the trunk to the left and right, aiming at transferring the weight in each of the lower limbs.
[figure not shown]	**4 minutes, 2×2 minutes**	In the sitting position, perform flexion and extension of both knees alternately.
[figure not shown]	**4 minutes, 2×2 minutes for each articulation**	In orthostatism, perform hip circumduction.
[figure not shown]	**4 minutes, 2×2 minutes for each articulation**	In orthostatism, perform abduction of both hips alternately.
[figure not shown]	**4 minutes, 2×2 minutes for each articulation**	In orthostatism, perform flexion of both hips alternately.
[figure not shown]	**4 minutes, 2×2 minutes for each articulation**	In orthostatism, initial position in hip flexion at 90°, perform knee flexion and extension.
[figure not shown]	**4 minutes, 2×2 minutes for each articulation**	Elevation of the lower limb forward (single leg support) during the horizontal shoulder abduction and adduction phase. Return to bipedal support during the horizontal shoulder abduction and adduction phase.
[figure not shown]	**4 minutes, 2×2 minutes for each articulation**	Hip flexion (single leg support) concomitant with shoulder extension followed by hip extension (bipedal support) concomitant with shoulder flexion.
[figure not shown]	**4 minutes, 2×2 minutes for each articulation**	Cross the forearms in front of the umbilical scar, followed by the horizontal flexion together with the movement of crossing one lower limb over the other.
[figure not shown]	**5 minutes**	Immersion in the whirlpool bath
**Fifteen seconds rest between each exercise** **Total program time: approximately 45 minutes**		

As a starting position to perform the exercises, the participants must remain in the semi-flexion position of their knees so that the water line must remain at shoulder height throughout the procedure. All the exercises will be performed according to the established time, and a 15-second rest time will be added between each exercise or series. As a manner of manipulating the intensity of the exercise at low intensity, the movement speed will be standardized according to the subjective sensation of effort according to Borg 6-20,
^
44
^ with zones of interest from 6 (extremely light) to 9 (very light). In this intervention modality, we will seek to understand the impact that the physiological effects of immersion in heated water pose on the studied variables.

Program B will consist of a sequence of exercises adapted from previous works
^
45
^
^,^
^
46
^ composed of warm-up, fortification, and cool-down activities. Aquatic steppes platforms will be used to ensure that all participants, when performing the exercises in orthostatism, will maintain the waterline level approximately at the level of the xiphoid appendix. For this program, the exercises will be performed at a speed that guarantees a comfortable water level for the activity, being the effort zones of interest from 10 (fairly light) to 14 (somewhat hard).

The warm-up sequence consists of four different active moves performed at maximum movement amplitude and contributes to neuromuscular activation.

After the warm-up, the participants will be submitted to the fortification program, which consists of a sequence of seven exercises aiming to promote muscular activation. The participants will be encouraged to perform the movement at a comfortable speed with the maximum possible movement amplitude. During sitting exercises, the need to maintain the lumbar spine in a neutral position will be emphasized in order to avoid overloading this segment.

To finish program B, as a way to calm down, a sequence of three activities will be performed, including a period in the hydromassage area, according to
Table 2.

**Table 2. T2:** Program B: medium-intensity protocol. The individuals in the images are students of the Physiotherapy course who consented and authorized their image.

Warm-up		
Exercise	Periodization	Description
[figure not shown]	**4 minutes**	Antero-posterior and latero-lateral walk.
[figure not shown]	**4 minutes**	Antero-posterior and latero-lateral walk with obstacles over 30-cm-steppes.
[figure not shown]	**1 minute**	Sitting and standing up.
[figure not shown]	**1 minute**	Skipping - running on the same place.
**Total warm-up time: approximately 10 minutes**		
**Fortification**		
[figure not shown]	**3 minutes**	In orthostatism with unipedal support of the lower limb contralateral to the moved segment, perform hip flexion and extension. The knee must remain in complete extension and the ankle in dorsiflexion. The lumbar spine must remain in a neutral position.
[figure not shown]	**3 minutes**	In orthostatism, perform hip abduction and adduction. The knee must remain in complete extension with the ankle in dorsiflexion. The movement must contemplate the maximum amplitude with the maintenance of the pelvis and lumbar spine in a static position.
[figure not shown]	**3 minutes**	In orthostatism, perform the movement of knee flexion and extension. The movement must contemplate the maximum flexion and extension with the maintenance of the lumbar spine in a neutral position.
[figure not shown]	**3 minutes**	In orthostatism, perform the wide movement of hip extension and knee flexion followed by hip flexion and knee extension (kick movement).
[figure not shown]	**3 minutes**	With the help of floats, perform the bicycle movement (alternating knee and hip flexion) aiming at the anterior displacement.
[figure not shown]	**3 minutes**	Patient in a supine position with the help of floats, perform the backstroke leg kick aiming at the cranial displacement.
[figure not shown]	**3 minutes**	In orthostasis, perform the slow walking movement, simulating a Nordic walk, sliding the feet on the bottom of the pool, however, without moving.
